
### Other data collected

In addition to the outcome measures, the following data will be collected in order to assess similarity between the treatment groups:

Intrinsic variables (baseline characteristics): age, gender, body mass index (BMI), American Society of Anesthesiologists (ASA) grade, tobacco consumption, comorbidities, and medication use.

Injury-related variables: injury mechanism, pleura drain placed, number and location of rib fractures, affected side, presence of sternum fracture, additional injuries represented by the Abbreviated Injury Score (AIS) [53], and Injury Severity Score (ISS).

Intervention-related variables: surgical approach, number of plates and splints used and for which ribs, surgical delay, primary and secondary surgeon (resident or staff surgeon), wound drain, intra-operatively placed interpleural drain including duration of drainage, and duration of surgery.

### Study procedures

Patients will be followed until 12 months after trauma. Clinical evaluation will occur daily during hospital admission. After discharge, outpatient clinic evaluation will occur at 2 weeks (window 7–21 days), 1 month (window 21–39 days), 3 months (window 11–15 weeks), 6 months (window 24–28 weeks), and 12 months (window 12–14 months). These visits are standard of care for the targeted patient group. A schedule of events is shown in Table 1. Baseline data and perioperative data will be collected from the patients’ medical files as soon as possible, but no later than the first outpatient department visit. At the 12-month follow-up contact, the surgeon or research assistant will document any secondary intervention that may be planned for the patient.

**Table 1 Tab1:** Schedule of events (duration after trauma)

Radiographs and event forms	Screening	Enrolment	Pre-surgery	Surgery	Post-surgery (until day 7*)	2 weeks (7–21 days)	30 days (21–39 days)	3 months (11–15 weeks)	6 months (24–28 weeks)	12 months^$^ (12–14 months)
CT-scan	X								X	
Screening	X									
Informed consent		X								
Randomization		X								
Baseline data			X	X						
Intervention/surgical report form				X	X					
Outpatient clinic FU						X	X	X	X	X
Spirometry							X	X	X	X
Analgesic use			Daily, afternoon		Daily, afternoon	X	X	X	X	X
Pain (NRS-rest and inspiration)			Daily, afternoon		Daily, afternoon	X**	X	X	X	X
Pain (NRS-night, daily, and care)						X**	X	X	X	X
QoL (EQ-5D and SF-12)						X**	X	X	X	X
Complications			X	X	X	X	X	X	X	X
(Secondary) interventions			X		X	X	X	X	X	X
iPCQ and iMCQ questionnaire						X***	X	X	X	X
Early withdrawal						****	****	****	****	****

*Post-surgery

^$^May be planned at the patients’ residency

**Asking for current and pre-trauma status

***Asking for pre-trauma situation

****Only if applicable.

After 6 months, a thoracic CT scan is repeated. Pulmonary function will be tested during the outpatient clinic visits at 1, 3, 6, and 12 months. At each follow-up visit, the coordinating researcher or research assistant will ascertain patient status (i.e., adverse events/complications or secondary interventions) and will verify information within the medical records. At each visit, patients will be asked to complete questionnaires relating to their pain (NRS), analgesics use, quality of life (QoL) (SF-12 and EQ-5D), and health care use (iPCQ and iMCQ).

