### Outcome measures

#### Primary outcome measure

The primary outcome measure is pneumonia within 30 days after trauma. In order to define pneumonia, the flowchart of the Centers of Disease Control and Prevention, based on imaging and clinical and laboratory criteria, will be followed (Fig. 1) [42]. Temperature (*T*) will be measured daily during admission. If *T* > 38.0 °C intra-auricular (or *T* > 39 °C rectal), bladder, central, or a sputum culture will be done. Also, the wound will be checked (if applicable) and a radiograph of the thorax will be made. If patients are suffering from fever at home, they will be advised to visit the outpatient clinic or emergency department. The temperature will be measured on arrival at the outpatient clinic or emergency department, and the same additional examinations will be performed. A monitor will independently review the patient’s medical files in order to ensure that the pneumonia was actually present.

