#### Secondary outcome measures

The secondary outcome measures are:Need and duration of mechanical ventilation in days. The number of days of invasive mechanical ventilation (by endotracheal tube or tracheostomy) from intubation until successful weaning will be determined. The need for mechanical ventilation will be evaluated based on arterial blood gas analysis and clinical performance of the patient. The duration of mechanical ventilation will be calculated from the dates of intubation and extubation. Re-intubation within 30 days will be recorded as well.Level of thoracic pain (NRS) and analgesics use. Thoracic pain will be determined using an 11-point Numeric Rating Scale (NRS) in which 0 implicates no pain and 10 the worst possible pain. Five thoracic pain levels will be analyzed: pain in rest, at night, during daily activities (e.g., work or hobbies), during maximal inspiration, and during self-care. Analgesics use during admission will be extracted from the medical files. After discharge, analgesics use will be asked for during the follow-up visits. Daily narcotic requirement will be calculated using an equivalence scale for 30 mg/day oral morphine.(Recovery of) pulmonary function. The parameters tidal volume (TV), forced vital capacity (FVC), inspiratory capacity (IC_lung_), and forced expiratory volume at 1 second (FEV_1_) will be determined using spirometry. Spirometry will be done by a member of the research team. During the spirometry, the patient has to inhale actively and exhale with maximum force possible. The mean of three tests will be calculated.Hospital length of stay expressed in days. This will be calculated as the time between admission and discharge from the hospital. Re-admission within 30 days will be added. Re-admission for thoracic reasons after 30 days and up to 12 months will be counted separately.ICU length of stay expressed in days. This will be calculated similarly to the hospital length of stay.Thoracic injury-related complications and mortality. The occurrence of thoracic injury-related complications will be recorded from the medical charts during clinical admission and each follow-up visit. Complications will be categorized for level of severity and treatment necessity according to the Clavien-Dindo classification [43]. Complications will include empyema (as diagnosed on CT scan, in presence of fever or positive cultures in the drained fluid), (retained) hydrothorax (a heterogeneous fluid collection with Hounsfield unit readings of 35–70 and evidence of pleural thickening) [44], nonunion (diagnosed on CT scan or operatively, at least 6 months after trauma) [45], and other (all other complications as judged by the treating physician). If mortality is caused by the thoracic injury or complication of thoracic injury, it will be counted in rates of mortality. Death caused by other reasons will be noted but excluded in this calculation.Surgery-related complications. The ORIF group can also develop hardware-related complications or failure. Hardware-related complication is superficial and deep wound infection which is defined as redness, tenderness, and warmth surrounding and in direct contact with the postoperative wound. Superficial infection leads to oral or IV antibiotics, and deep infection leads to surgical activity such as stitch removal of exploration of the wound. Hardware failure is defined as loosening of the plate, secondary dislocation of fixation material, malposition of hardware, and broken plates or splints.Secondary interventions to resolve complications. Secondary interventions within 12 months after trauma to relieve pain, treat infection, or other rib fracture-related problems will include the following: antibiotic therapy (both oral and intravenous), additional surgical interventions (e.g., surgical stabilization of nonunion, evacuation of hematoma, evacuation of empyema, removal of failed hardware, symptomatic hardware removal, and treatment of infection), and additional percutaneous interventions (e.g., for persistent bleeding intercostal artery, intraparenchymal bleeding, drainage of infection, and drainage of pleural fluid).Health-related quality of life measured using the Short Form-12 (SF-12) and EuroQoL-5D (EQ-5D) questionnaires. The SF-12 analyzes global health status, functional scale, and symptom scale. The score will be calculated based on eight domains and summarized into a Physical Component Summary (PCS) and Mental Component Summary (MCS). Data will be reported as utility score, ranging from 0 to 1 with a higher value indicating better quality of life. As a reference, the US population of 1998 will be used [46]. The EQ-5D is the most commonly used quality of life instrument for (rib) fracture patients [47, 48]. The EQ-5D is recommended for assessment of quality of life in trauma patients, especially for economic evaluation [49, 50]. The EQ-5D-5 L descriptive system consists of five dimensions of health (mobility, self-care, usual activities, pain/discomfort, and anxiety/depression), each with five possible answers. The patients’ health states will be converted into a utility score using the Dutch tariff [51]. Utility scores range from 0 to 1 with lower scores indicating poorer quality of life.Cost-effectiveness and health care consumption. Economic evaluations will be done from a societal perspective. The validated Medical Consumption Questionnaire (iMCQ) and Production Consumption Questionnaire (iPCQ) will be used. iMCQ details medical specialist care, physical therapy, hospitalization, nursing home, home care, and other costs directly associated with diagnosis, treatment, and rehabilitation. iPCQ comprises work resumption and production losses. Health care costs and lost productivity until 1 year after trauma will be measured in accordance with economic guidelines [52].

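### Table 1 lets the only follow-up CT take place before nonunion can be diagnosed under the protocol's own definition; a lesser point is that the 30-day visit may precede day 30

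*Protocol article*

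**What the plan says.** **Nonunion and the CT.** In the protocol article, the Secondary outcome measures section lists among the thoracic complications "nonunion (diagnosed on CT scan or operatively, at least 6 months after trauma"). The running text of Study procedures states: "After 6 months, a thoracic CT scan is repeated". The same section gives the visit windows as "1 month (window 21–39 days), 3 months (window 11–15 weeks), 6 months (window 24–28 weeks"). Table 1 marks CT twice only, at screening and at the 6-month visit. Its title, "Schedule of events (duration after trauma"), fixes the time origin as trauma, which is also the origin in the nonunion definition.

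**The 30-day outcomes.** The Primary outcome measure section states: "The primary outcome measure is pneumonia within 30 days after trauma". Re-admission and re-intubation are also recorded over 30 days (Secondary outcome measures). The visit nearest that point is given in the text as "1 month (window 21–39 days") and in Table 1 as "30 days (21–39 days"). The next scheduled visit is at 11 to 15 weeks.

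**Other capture of pneumonia.** Temperature is taken daily in hospital. Patients with fever at home are advised to attend, and the same examinations are then done. A monitor reviews the medical files independently (Primary outcome measure). At every follow-up visit, complications are asked about and checked against the records (Study procedures).

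**The concern.** The CT issue is an internal inconsistency. A site that follows Table 1 exactly can scan a patient in week 24 or 25. If that scan shows an unhealed fracture, it is too early to count as nonunion under the outcome definition, and the schedule holds no later scan that could settle it. The patient is then either left out of the nonunion count or counted against the definition. The nonunion rate would depend partly on when in the window the scan happened to be done, and partly on how each site resolved the conflict.

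The visit issue is a weakness of timing and not a contradiction. A patient seen on day 21 has not yet completed the period over which the primary outcome is counted, and the next scheduled contact is weeks away. At stake is late pneumonia that leaves no trace in the trial hospital's files, or that occurs in a patient who never returns for the 3-month visit.

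**Working it through.** The plan states no figure of its own on this point, so there is none to reproduce. The check is calendar arithmetic on the stated windows.

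**Inputs**
- CT window: 24 to 28 weeks after trauma (Study procedures, Table 1).
- Nonunion threshold: at least 6 months after trauma (Secondary outcome measures).
- Visit window: days 21 to 39 after trauma (Study procedures, Table 1).
- Primary outcome period: 30 days after trauma (Primary outcome measure).
- Calendar: start dates from 2019 to 2021, matching the January 2019 start and three-year recruitment in Trial status.

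**CT against the nonunion threshold**
1. The window opens on day 24 × 7 = 168 and closes on day 28 × 7 = 196. It has 196 − 168 + 1 = 29 permitted days.
2. Over all start dates in 2019 to 2021, six calendar months last between 181 and 184 days.
3. The window therefore opens 181 − 168 = 13 to 184 − 168 = 16 days early.
4. Permitted days before the threshold:

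| Reading of 6 months | Days too early | Share of 29 |
|---|---|---|
| 180 days | 12 | 41% |
| 181 days (shortest calendar) | 13 | 45% |
| 184 days (longest calendar) | 16 | 55% |

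5. Starting at 26 weeks would not fully cure this: 26 × 7 = 182 days, which can still fall short of six calendar months when these last up to 184 days.

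**Visit against day 30**
1. The window has 39 − 21 + 1 = 19 permitted days. Days 21 to 29 are 9 of them, 9/19 = 47%.
2. A visit on day 21 leaves 30 − 21 = 9 days to run, 9/30 = 30% of the period.
3. The next visit falls between day 11 × 7 = 77 and day 15 × 7 = 105, which is 56 to 84 days after a day-21 visit.

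These shares count permitted days. They are not the expected share of scans or visits, nor a share of pneumonia risk, because the document does not say how scans, visits or events are spread in time.

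**The case against.** **On the CT.** The running text shows that a scan after six months was intended, and 24 to 28 weeks is 26 ± 2 weeks, an ordinary tolerance around a nominal six-month visit. Nonunion may also be diagnosed operatively, and complications are recorded up to 12 months, so a patient scanned early can still be diagnosed later. Both arms share the window, and nonunion is one component of a secondary outcome. All of this stands, and it limits the weight of the point. It does not remove the conflict: the table permits scans that the text and the definition exclude, and later confirmation would depend on an operation or an unscheduled scan. The 12-month window in the same table (12 to 14 months) does not open early.

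**On the visit.** A reader might infer that this visit closes the primary outcome, so that an early visit leaves pneumonia status missing. The document does not support that. No section gives the visit that role. Pneumonia is an event defined by imaging, clinical and laboratory criteria, so it should leave dated records, and the fever route, the monitor's review and the record checks at later visits all cover days 22 to 30. What remains is narrower. The fever route relies on the patient attending. Record checks may not find pneumonia treated elsewhere. The 3-month visit cannot help for patients lost before it.

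A reader might also infer bias in favour of surgery, since the Discussion hopes for a shorter stay after fixation and operated patients might then be at home more often in these days. The direction is conceivable, but nothing in the document gives its size or shows that it occurs. The 25% allowance in the Sample size calculation covers loss to follow-up and mortality together and does not say how many patients are lost between these two visits.

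**Conclusion.** The CT point holds as an inconsistency between Table 1, the running text of Study procedures and the nonunion definition. Of the 29 permitted days, 13 to 16 come before six calendar months (12 if six months is read as 180 days), and no later CT is scheduled. This assumes that the windows run from trauma, as the title of Table 1 says. It affects one component of a secondary outcome; the primary analysis is untouched and no difference between arms is shown.

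The visit point holds only as a lesser weakness. The visit may precede the end of the pneumonia period by up to 9 days, and capture of late events then rests on routes that recover many but not reliably all of them. The same applies to re-admission and re-intubation if their 30 days also run from trauma, which the article does not state. The number of events at risk cannot be derived from the document, and missing data for the primary outcome is not shown.

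**What to change.** **CT.** Reconcile Table 1, the running text and the nonunion definition in one of two ways:
- State that a CT used for the nonunion outcome may not precede the six-month threshold, and express the threshold and the window in the same unit. The cost is a tighter schedule: if the upper limit stays at day 196, 29 − 16 = 13 to 29 − 13 = 16 permitted days remain.
- Keep the window and state in advance how an unhealed fracture on a CT before six months is classified. This costs one sentence and no scheduling change, but those patients' status would rest on the stated rule, because no later scan is scheduled.

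**30-day outcomes.** Keep the day 21 to 39 window. Moving it later would also shift the spirometry, pain, quality-of-life and cost measures taken at that visit, a trade-off this point does not justify. For patients seen before day 30, add a brief phone or record check at or after day 30 to confirm 30-day outcome status. A phone contact also asks about treatment elsewhere, which a local file check may not show. The cost is one short contact or file check for those patients only, with no extra clinic visit or scan.

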### Sample size calculation

Calculation of the required sample size for the primary analysis is based on data from a Cochrane review and a large retrospective analysis [7, 32]. These studies suggest a pneumonia rate of 35% in nonoperatively treated patients and 15% in operatively treated patients with multiple rib fractures. This difference is considered clinically relevant. A two-sided test with an α level of 0.05 and a β level of 0.2 requires 72 patients in each group. In order to account for 25% loss of patients to follow-up and mortality, a sample size of 90 patients per group is needed. In total, 180 patients will be included and randomized.

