### Recruitment and randomization

Eligible persons presenting to the emergency department (ED) or referred from another hospital, with multiple, simple rib fractures will be informed about the trial at the ED or at the surgical ward after admission. After explanation of the study, eligible patients will receive written information and a consent form from the attending physician, the clinical investigator, or a research assistant. Patients meeting all eligibility criteria will be recruited within 1 day after hospital admission. As surgical rib fixation appears to be most beneficial when performed within 72 h after trauma, patients are stimulated to decide within this period. However, informed consent can be given by the patient as long as rib fixation can be carried out within 1 week after trauma. Should patients not be able to sign informed consent themselves, a legal representative will receive oral and written information about the study, in the hospital, by the attending physician, the clinical investigator, or a research assistant, and will be asked to consent with participation of the patient.

After signing informed consent by patient or proxy, participants are allocated to one of the two study arms (surgical stabilization or nonoperative treatment) using a web-based randomization program that will be available 24 h a day. Allocation will be at random and concealed, in a 1:1 ratio, and will be stratified by site. Variable block sizes will be used; in each block, both treatments will be represented equally. As the intervention cannot be blinded, it will in no case be necessary to break the randomization code.

As with many surgical trials, patients and surgeons cannot be blinded for the intervention. In order to reduce bias as much as possible, a research physician or research assistant will perform the follow-up measurements using a standardized protocol. Also, the treating surgeon or ICU doctor will identify the primary outcome (i.e., pneumonia) based on the definition as mentioned under outcome measures.

Participation is on a voluntary basis and participants are allowed to withdraw from the study at any time without specifying why. The general practitioner will be informed about the patients’ participation.

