### Statistical analyses

Data will be analyzed using the Statistical Package for the Social Sciences (SPSS), version 24.0 or higher (SPSS, Chicago, IL, USA), and reported following the Consolidated Standards of Reporting Trials (CONSORT) guidelines. Normality of continuous data will be tested with the Shapiro-Wilk test. Homogeneity of variances will be tested using Levene’s test. The analysis will be performed on an intention to treat basis. A two-sided *p* value < 0.05 will be taken as threshold of statistical significance in all statistical tests. Procedures will be implemented to reduce missing data. In previous studies of the principal investigator’s department, these procedures led to < 5% missing data [54]. If necessary, missing values will be replaced using multiple imputation following the predictive mean matching method, using ten imputations.

Descriptive analysis will be performed in order to report the outcome measures for both treatment arms. For categorical data, numbers and frequencies will be reported. For continuous data, the mean and SD (parametric data) or the mean and percentiles (non-parametric data) will be reported.

Next, univariate analysis will be performed in order to test for statistical significance of differences between the primary and secondary outcome measures across the two groups. A chi-squared analysis or Fisher’s exact test will be used for statistical testing of categorical data (e.g., the primary outcome, pneumonia). Continuous data (i.e., hospital length of stay) will be tested using Student’s *t* test (parametric data; with equal variance or unequal variance whichever applies according to Levene’s test) or Mann-Whitney *U* test (non-parametric data).

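### The allowance for 25% loss multiplies 72 by 1.25 instead of dividing by 0.75, so 90 per group covers only 20% loss and gives about 77% power, not 80%, if 25% are lost

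*Protocol article*

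**What the plan says.** The protocol article, under *Sample size calculation*, gives the planning rates: "These studies suggest a pneumonia rate of 35% in nonoperatively treated patients and 15% in operatively treated patients with multiple rib fractures". The base requirement follows: "A two-sided test with an α level of 0.05 and a β level of 0.2 requires 72 patients in each group". The allowance for loss is then applied: "In order to account for 25% loss of patients to follow-up and mortality, a sample size of 90 patients per group is needed". The total is stated as: "In total, 180 patients will be included and randomized". Under *Recruitment and randomization*, allocation is 1:1.

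Under *Ethical concerns*, the article says that participants who leave are not replaced, and that the expected loss has been built into the sample size. The inflation step is therefore the only protection against loss that works through patient numbers.

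**The concern.** Three figures in one short paragraph do not fit together: 72 needed, 25% lost, 90 enough. A loss percentage is a share of the patients enrolled. To end with 72 after losing a quarter, the enrolled number times 0.75 must equal 72. The article's 90 is instead 72 plus a quarter of 72, a common slip.

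At stake is the stated justification of the trial's size for its primary outcome. If the planned loss did occur, the type II error would exceed the stated 0.2, and the sentence that claims to cover that loss would be untrue.

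**Working it through.** **Inputs** (all from *Sample size calculation*, except the allocation ratio from *Recruitment and randomization*): p1 = 0.35, p2 = 0.15, difference 0.20, mean rate 0.25; two-sided α = 0.05 (z = 1.960); β = 0.2 (z = 0.842); loss 25%; 1:1 allocation.

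**Step 1: reproduce the base figure.** For the uncorrected chi-squared test with pooled variance under the null:

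n = [1.960 × √(2 × 0.25 × 0.75) + 0.842 × √(0.35 × 0.65 + 0.15 × 0.85)]² / 0.20²
= [1.960 × 0.6124 + 0.842 × 0.5958]² / 0.04
= 1.7017² / 0.04 = 72.4.

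The stated 72 is this figure rounded down (rounded up it would be 73). Other usual formulas give 69.7 (unpooled) and 70.9 (arcsine). The base figure is sound.

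**Step 2: the loss allowance.**

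| Calculation | Result |
|---|---|
| 72 × 1.25 | 90 per group, 180 in total (the article's figures) |
| 72 / (1 − 0.25) | 96 per group, 192 in total |
| 90 × (1 − 0.25) | 67.5 per group remaining |
| 1 − 72/90 | 20%, the largest loss at which 90 still leaves 72 |

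Changing the base formula does not close the gap: the smallest base figure in step 1, 69.7, is still above 67.5.

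**Step 3: power with what remains.** With the pooled formula, power = Φ[(0.20 × √n − 1.960 × 0.6124) / 0.5958].

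| Patients per group | Power, pooled formula |
|---|---|
| 72 | 79.8% |
| 68 | 77.4% |
| 67.5 | 77.1% |
| 67 | 76.8% |

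At 67.5 per group the arcsine formula gives 78.1% and the unpooled formula 78.8%. Exact enumeration of the uncorrected chi-squared test gives 77.5% at 67 and 78.3% at 68, against 81.0% at 72. The result is about 77% to 79%, so the shortfall from 80% is about 1 to 3 percentage points.

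**Step 4: how it depends on the loss** (90 randomised per group, pooled formula).

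| Loss | Remaining per group | Power |
|---|---|---|
| 5% | 85.5 | 86.2% |
| 10% | 81 | 84.3% |
| 20% | 72 | 79.8% |
| 25% | 67.5 | 77.1% |

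**The case against.** The strongest reply is that 25% of patients are unlikely to lack the primary outcome. Pneumonia is recorded up to 30 days after trauma, with daily evaluation in hospital and visits at 2 weeks and 1 month, whereas follow-up runs to 12 months. The 25% is described as loss to follow-up and death in general, not as missing 30-day data. Under *Statistical analyses*, the article reports less than 5% missing data in the department's earlier studies, and it plans multiple imputation if needed. This stands as a limit on the practical harm: on those figures the trial probably keeps 80% power. It does not make the sentence correct, because 25% is the article's own planning figure. Nor does imputation in general restore the information in outcomes that were never observed.

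Two stronger readings are tempting, and the article supports neither.

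- **That the trial is underpowered and must enrol 192.** The shortfall is small and arises only if the loss of the 30-day outcome exceeds 20%. A corrected statement of what 180 patients deliver is enough.
- **That Fisher's exact test makes the shortfall larger.** *Statistical analyses* names chi-squared or Fisher's exact test in a general sentence on categorical data, with pneumonia as the example. The article does not claim that 72 per group gives 80% power with Fisher's test. That test is ordinarily the fallback for small expected counts. Here, with 67 per group and a mean rate of 25%, about 17 pneumonia cases per group are expected (67 × 0.25 = 16.75). The rule for choosing between the two tests can properly be left to an analysis plan that is not shown. Fisher's test is no part of this error.

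**Conclusion.** The sentence is wrong as written: 90 per group does not account for 25% loss from a requirement of 72. It accounts for 20%. Under the stated 25% loss, power is about 77% rather than 80%, or about 77% to 79% depending on the formula.

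This rests on the article's own rates of 35% and 15%, two-sided 0.05, an uncorrected chi-squared test, equal loss in both groups, and an analysis of patients with an observed outcome. The base figure of 72 is not in question. The error is certain and easily checked by hand, but its consequence is modest and conditional on heavy loss of a 30-day outcome. It calls for a correction to the stated justification, not a change to the design.

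**What to change.** Keep 180 patients and replace the sentence on loss with one of two consistent statements:

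- With 25% loss, about 67 patients per group remain, giving about 77% power for 35% versus 15% (uncorrected chi-squared, two-sided 0.05).
- Ninety patients per group retain 72 evaluable patients for losses of up to 20%.

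The first keeps the 25% planning figure and is open about its effect. The second describes what 90 covers; it should not be presented as a new forecast of loss, because nothing in the article supports 20% as an expectation. Either can be followed by a remark that at 5% loss about 85 per group remain and power is about 86%.

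The cost is one corrected sentence and, with the first option, a slightly lower stated power. No extra patients are needed and the analysis does not change. Only if both 25% loss and 80% power are to be kept does the number become 96 per group, 12 more patients in total.
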